**Figure 3 figure3:**
[figure not shown]
Pilot study flow and assessments. EMR: electronic medical record; *iARTs*: i.ART+support; LAI ART: long-acting injectable antiretroviral therapy.

### Phase 3: Pilot Test *i.ARTs*

#### Study Design

Phase 3 will pilot test the final *i.ARTs* patient decision aid to assess feasibility, acceptability, and usability as well as to evaluate associations between receipt of *i.ARTs* and ART adherence, including viral suppression, ART refills, chosen ART modality, and clinic attendance. The pilot will be a 2-arm randomized controlled trial with 180 WWH. It will compare an intervention arm (n=90 WWH) that uses the *i.ARTs* decision aid tool developed in phases 1 and 2 with a standard-of-care control arm (n=90 WWH).

#### Setting, Participants, Recruitment, and Enrollment

Pilot testing will occur among WWH at the same Miami MWCCS clinical site where phase 2 focus groups occurred. The clinic is one of the largest hospital-based clinics in Miami, a city with one of the highest rates of incident and prevalent HIV infections in the United States. We will recruit 180 women from the existing client population over the course of 15 months (about 12 women per month). A full-time research associate will approach potential participants at their regular clinic visit, share information about the study, and invite them to take part in eligibility screening. Participants must meet the following eligibility criteria: (1) identify as female; (2) be receiving HIV-related care at the Miami site; (3) have a diagnosis of HIV infection; (4) aged 18 and older; (5) be interested in learning about LAI ART and open to discussing HIV treatment with their provider; and (6) be willing to provide informed consent.

#### Study Procedures

##### Randomization

Following informed consent and the baseline assessment (discussed later), we will use a web-based system to randomize women (1:1) to the *i.ARTs* intervention arm (n=90) or to the standard-of-care control arm (n=90). Neither participants nor researchers will be blind to study condition. Women in the control arm will receive standard of care as it exists at the time of LAI ART roll out: providers will offer women information about LAI ART and may strongly suggest which option she should choose. Women who participated in the focus groups will not be eligible for inclusion.

Women in the intervention arm will use *i.ARTs* as part of their regular participant visit. While the complete content of *i.ARTs* will be finalized in phase 2, the web-based *i.ARTs* app will guide WWH through the following activities: (1) provide education on different ART modalities, (2) utilize value clarification methods to guide women in ranking the prominence of relevant barriers and facilitators that may impact adherence to various ART modalities, (3) collect information on participant health history, (4) generate a suggested ART modality based on previous steps, (5) assist WWH in developing questions for their health care providers, and (6) generate an individual profile description as well as individualized suggestions to support adherence based on the modality selected (eg, a woman may be profiled as having transportation challenges; *i.ARTs* would suggest solutions—arranged transportation or transportation vouchers—that the clinic could employ to address these challenges). Participants will take a printout of this profile to their clinic visit with their provider. Intervention arm participants will receive US $15 for *i.ARTs* use.

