##### Assessments

All women enrolled in the study will complete a baseline survey following informed consent and a follow-up survey immediately after their clinical visit. Surveys will be administered on tablets in a private room within the clinic and will use REDCap for data collection. Each survey will take approximately 25 minutes to complete, and women will receive US $25. Survey measures are described later and in Table 2.

A subsample of 20 intervention (*i.ARTs*) arm women and 10 providers will be randomly chosen to participate in an exit interview. This interview will occur either at the baseline visit or up to 1 month after *i.ARTs* use at the participant’s convenience. We will select every fourth woman in the intervention arm to complete the exit interview. Providers will be selected based on the number of *i.ARTs* participants they served in the first year of the pilot (we will randomly select 10 providers from all providers who serve above the median number of *i.ARTs* clients, which ensures that providers will have sufficient experience with the tool to provide feedback) and exit interviews with providers will be conducted in the final 3 months of data collection. These interviews will focus on patient and provider experiences with *i.ARTs* acceptability, feasibility, and usability, and the most useful ways to improve its integration into clinical practice. This will also include discussions of how women shared the results from the patient decision aid with their provider. Exit interviews will take approximately 30 minutes and participants will be provided US $30 in compensation.

The study will also use all 180 participants’ electronic medical records (EMRs) to assess the impact of the intervention on clinical outcomes (Table 2). The informed consent process will include the EMR abstraction release form and detailed information about the data abstraction process. Study staff will abstract data on viral suppression (all women), ART modality, clinic attendance (all women), and medication refill data (women on oral ART) from EMRs into a REDCap database. Abstraction will include data from 1-year prebaseline to 6 months postbaseline. This timeline is based on the frequency of HIV clinic visits (ie, approximately every 3 months) to ensure that women have at least one visit in the follow-up period.

**Table 2 table2:** *i.ARTs*^a^ pilot study measures in phase 3.

Outcomes			Description of measures

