**Primary**			Assessed after *i.ARTs* use among women using i.ARTs (n=90)
	Feasibility	Adaptation of Thabane et al’s [59] framework [60,61] for assessing pilot studies: Process, Resources, Management, Science	
	Acceptability and usability	Acceptability [62] and CSQ-8^b^ [63] to measure satisfaction with *i.ARTs*; exit interviews about *i.ARTs* features/protocol [62]	
**Secondary**			Assessed in baseline survey and postvisit survey for all women (n=180)
	Decisional conflict	Decisional Conflict Scale (16 items) [52]; satisfaction with the chosen method [64]	
**Tertiary**			Assessed 1-year prebaseline, at baseline, 3 months, and 6 months (all women; n=180)
	Viral suppression	Viral suppression, defined as viral load below limit of detection per assay used	
	Medication refills	Missed doses; report of medication refills/pharmacy pick up (WWH^c^ on oral ART^d^)	
	Clinic attendance	Missed or cancelled medical visits (<2 visits in a 6-month period for oral ART; missed monthly visit for LAI^e^ ART)	
	ART modality	Adoption of LAI among patients who are virally suppressed	
**Moderators**			Assessed at baseline
	Sociodemographics	Race/ethnicity, age, housing stability, education, employment, income, distance from clinic, relationship status, children	
	Depression/anxiety	PHQ-8^f^ (depression) [65]; GAD-7^g^ [66]	
	Substance use	ASSIST^h^ [67], an 8-item measure of problematic substance use	
	Stigma/discrimination	MDS^i^ to measure racial discrimination [68]; HIV-related stigma	
	Self-efficacy	HIV-ASES^j^ [38]	
	ART-related knowledge	Adaptation of Feldman’s [69] scale of oral ART knowledge; BMQ^k^ [70]	

^a^*i.ARTs*: i.ART+support.

^b^CSQ-8: 8-item Client Satisfaction Questionnaire.

^c^WWH: women with HIV.

^d^ART: antiretroviral therapy.

^e^LAI: long-acting injectable.

^f^PHQ-8: 8-item Patient Health Questionnaire.

^g^GAD-7: 7-item General Anxiety Disorder scale.

^h^ASSIST: Alcohol, Smoking and Substance Involvement Screening Test.

^i^MDS: 10-item Multiple Discrimination Scale.

^j^HIV-ASES: HIV Treatment Adherence Self-Efficacy Scale.

^k^BMQ-18: 18-item Beliefs and Medicines Questionnaire.

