#### Analysis

The primary outcomes of feasibility, acceptability, and usability will be assessed descriptively. We will compare ART-related decisional conflict, clinic attendance, viral suppression, and medication refills between and within the 90 women in each arm (baseline vs postvisit surveys and EMR data at 3 and 6 months). For normally distributed data, we will first use *t* tests to compare the 2 arms and then use regression methods to develop a multivariable model of the outcome, with arm membership as the principal covariate, while controlling for the moderators listed in the previous sections and in Table 2. For nonnormally distributed data, we will employ chi-square tests and logistic regression; distributional properties of the outcome will determine the type of logistic regression (eg, binary, multinomial, or ordinal logistic regression models). We note that these are examples and the final approach will be determined based on the distribution of the data.

The primary analysis will use an intent-to-treat approach with the use of *i.ARTs* as a 1-time exposure, with α=.05, and 2-sided tests. The number of moderators included in the regression model will be used to make a Bonferroni adjustment to the α value. A secondary efficacy analysis will explore actual treatment taken. Our exploratory tertiary outcomes of viral suppression, clinic attendance, chosen ART modality, and medication refills will compare both between and within *i.ARTs* and control arm women (ie, baseline and postvisit surveys and EMR data at 3 and 6 months); we will also examine these outcomes for women who do not change regimens. We will use prebaseline EMR data to control for previous viral load. We will also compare how many women in each arm change modalities postbaseline to assess *i.ARTs’* accuracy in identifying which HIV treatment modality is the best match. Sensitivity analyses will determine whether assumptions associated with each model are defensible.

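### The unqualified statement that no researcher is blind also covers chart abstraction and choice of the final model, two steps where arm could be masked

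*Protocol article*

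**What the plan says.** All references are to the protocol article.

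- **Blinding (Randomization).** "Neither participants nor researchers will be blind to study condition". No exception is made for outcome abstractors or the analyst.
- **Who collects the record outcomes (Assessments).** "Study staff will abstract data on viral suppression (all women), ART modality, clinic attendance (all women), and medication refill data". The refill item is restricted to women on oral ART. The data go into a REDCap database.
- **How the outcomes are defined (Table 2, tertiary rows).** Medication: "Missed doses; report of medication refills/pharmacy pick up". Attendance: "Missed or cancelled medical visits (<2 visits in a 6-month period for oral ART; missed monthly visit for LAI", the last being LAI ART. Suppression: "Viral suppression, defined as viral load below limit of detection per assay used".
- **Status (Study Outcomes and Measures).** The record-based outcomes are tertiary and labelled exploratory. Decisional conflict is the secondary outcome, and Power Analysis and Sample Size bases the sample size on it.
- **Model choice (Analysis).** t tests, chi-square tests and several regression types are named, followed by: "We note that these are examples and the final approach will be determined based on the distribution of the data".

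**The concern.** Lack of masking is unavoidable for the women who use the tool and for the providers who receive its printout. It is not unavoidable for a person copying visit and refill dates out of a chart weeks later, or for a person deciding whether a score should be analysed as continuous or in categories. The Randomization sentence nevertheless covers everyone on the research side.

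Two biases become possible. An abstractor who knows the arm may resolve an unclear record in the direction she expects. An analyst who knows the arm may prefer, without intending to, the form of analysis that shows a difference. The second matters more than its place in the outcome hierarchy suggests, because decisional conflict is the outcome for which the trial was sized.

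The record outcomes also deserve protection because the other between-arm measure, decisional conflict, is self-reported by women who know their arm. The primary outcomes are descriptive and measured only among i.ARTs users, so this point does not touch them.

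**Working it through.** The plan gives no figure for this point, and masking changes no sample size. The check is mainly a reading of the passages side by side, followed by two illustrations of direction.

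**1. Which abstracted items leave room for judgement**

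- *Viral suppression*: an assay threshold. Little room.
- *ART modality*: a recorded treatment. Little room. The abstractor must see it, but modality is not the same as arm.
- *Which visit counts for suppression*: Study Outcomes and Measures takes the latest visit in the preceding half-year, which a date settles.
- *Clinic attendance*: Table 2 counts cancelled as well as missed visits and gives count rules for each modality, so that distinction is settled. It does not say how a cancelled visit that was rescheduled and kept is handled. Some room.
- *Missed doses and refills*: Table 2 lists missed doses. The abstraction list in Assessments names refill data only, and no rule says what counts as a missed dose in a chart. Most room.

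Abstraction bias is therefore confined mainly to missed doses and refills and to rescheduled visits.

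**2. What the model choice can reach**

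The open choice in Analysis applies to every compared outcome, including decisional conflict. That score runs from 0 to 100 with interpretive bands ending at 25 and starting at 37.5, so both a continuous and a categorical analysis are available. The power calculation assumes a two-sample t test. The plan's stated criterion is the distribution of the data. Whether that is judged pooled or by arm is not said.

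**3. Illustration for abstraction (assumed inputs)**

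One reclassified record moves an arm's attendance rate by 1/90 = 1.1 points. For refills the denominator is the number of women on oral ART, which is unknown, so the shift per record is at least that.

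Suppose no true effect, 90 per arm, and a 35% event rate (the article's national non-adherence figure, borrowed only for scale). Suppose also that a fraction m of intervention-arm events goes unrecorded. Then p₂ = 0.35(1 − m) and d = 0.35 − p₂. With p̄ = (0.35 + p₂)/2, se₀ = √(2p̄(1 − p̄)/90) and se₁ = √((0.35×0.65 + p₂(1 − p₂))/90), the two-sided rejection rate is Φ((d − 1.96se₀)/se₁) + Φ((−d − 1.96se₀)/se₁).

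For m = 20%: p₂ = 0.28, d = 0.07, se₀ = 0.0692, se₁ = 0.0690, giving 0.171 + 0.001 = 17.2%.

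| m | Spurious difference (points) | Rejection rate |
|---|---|---|
| 0 | 0 | 5.0% |
| 5% | 1.8 | 5.7% |
| 10% | 3.5 | 7.9% |
| 20% | 7.0 | 17.2% |
| 30% | 10.5 | 33.7% |

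Nothing in the article indicates a value of m.

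**4. Illustration for model choice (assumed behaviour)**

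A null simulation used 10,000 runs, 90 per arm, and normal scores with the control-arm planning values (mean 28, SD 18) limited to 0–100. Used alone, the t test, the chi-square cut at 25 and the chi-square cut at 37.5 rejected in 5.1%, 4.9% and 4.8% of runs. Reporting the better of the t test and the cut at 25 gave 7.8%. The best of all three gave 10.3%. The plan does not propose choosing by result. The figures show only what is lost if the choice is made with arm differences in view.

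**The case against.** The strongest reply is that a condensed article leaves the choice of model, and the data on which it is made, to an analysis plan that is not shown, and that open model choice is a question of prespecification rather than of blinding. That has force, and the absence of such detail is not itself criticised here. What remains is what the article states: an unqualified sentence that researchers are not blind, and a final method to be settled from the data.

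Three stronger readings are tempting, and the article does not support them.

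- *That the tool's developers abstract the charts.* It says only study staff.
- *That the model is chosen with results by arm visible.* It speaks of the distribution of the outcome and the data, and a pooled check fits that wording.
- *That a definite bias can be quoted.* Assuming 10% unclear records (9 per arm) with half resolved favourably in one arm gives 4.5/90 = 5 points. That depends on an invented rate, on control records not being resolved in the same way, and on a denominator of 90 that does not fit the oral-ART-only refill outcome.

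It is also fair to say that masking may fail in practice. One full-time research associate approaches the women, and if that person also abstracts, hiding a database field conceals little. Programmed derivation does much of the work without masking. This limits what masking can achieve but does not remove the case for it.

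**Conclusion.** The point stands as a modest, inexpensive improvement. The article states that no researcher is blind, although arm could be masked at manual record abstraction and at choice of the model form. The abstraction part affects tertiary, exploratory outcomes, chiefly missed doses and refills and the handling of rescheduled visits. The model-choice part extends to decisional conflict. The size of any bias cannot be estimated from the document, and the illustrative figures depend on the assumptions stated with them. The conclusion also assumes that the word researchers includes abstractors and analysts, which its unqualified use implies but does not spell out.

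**What to change.** - **Blinding sentence.** Limit it to participants, providers and staff who deliver i.ARTs.
- **Abstraction.** Use a REDCap form with the arm hidden. Enter only raw dates and values: scheduled and kept visits, fill dates, viral loads. Derive attendance, refill and suppression outcomes by program under written rules that cover rescheduled visits. State whether missed doses are derived from fill dates or come from another named source.
- **Model choice.** Choose the model form on data pooled over arms, and record the choice before the arm code is merged.

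The cost is REDCap user rights and a short derivation program, with no extra staff. Masking will be imperfect where the abstractor also enrolled the woman or the chart mentions i.ARTs, but programmed derivation still limits arm-aware judgement in those cases.

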##### Assessments

All women enrolled in the study will complete a baseline survey following informed consent and a follow-up survey immediately after their clinical visit. Surveys will be administered on tablets in a private room within the clinic and will use REDCap for data collection. Each survey will take approximately 25 minutes to complete, and women will receive US $25. Survey measures are described later and in Table 2.

A subsample of 20 intervention (*i.ARTs*) arm women and 10 providers will be randomly chosen to participate in an exit interview. This interview will occur either at the baseline visit or up to 1 month after *i.ARTs* use at the participant’s convenience. We will select every fourth woman in the intervention arm to complete the exit interview. Providers will be selected based on the number of *i.ARTs* participants they served in the first year of the pilot (we will randomly select 10 providers from all providers who serve above the median number of *i.ARTs* clients, which ensures that providers will have sufficient experience with the tool to provide feedback) and exit interviews with providers will be conducted in the final 3 months of data collection. These interviews will focus on patient and provider experiences with *i.ARTs* acceptability, feasibility, and usability, and the most useful ways to improve its integration into clinical practice. This will also include discussions of how women shared the results from the patient decision aid with their provider. Exit interviews will take approximately 30 minutes and participants will be provided US $30 in compensation.

The study will also use all 180 participants’ electronic medical records (EMRs) to assess the impact of the intervention on clinical outcomes (Table 2). The informed consent process will include the EMR abstraction release form and detailed information about the data abstraction process. Study staff will abstract data on viral suppression (all women), ART modality, clinic attendance (all women), and medication refill data (women on oral ART) from EMRs into a REDCap database. Abstraction will include data from 1-year prebaseline to 6 months postbaseline. This timeline is based on the frequency of HIV clinic visits (ie, approximately every 3 months) to ensure that women have at least one visit in the follow-up period.

**Table 2 table2:** *i.ARTs*^a^ pilot study measures in phase 3.

Outcomes			Description of measures
**Primary**			Assessed after *i.ARTs* use among women using i.ARTs (n=90)
	Feasibility	Adaptation of Thabane et al’s [59] framework [60,61] for assessing pilot studies: Process, Resources, Management, Science	
	Acceptability and usability	Acceptability [62] and CSQ-8^b^ [63] to measure satisfaction with *i.ARTs*; exit interviews about *i.ARTs* features/protocol [62]	
**Secondary**			Assessed in baseline survey and postvisit survey for all women (n=180)
	Decisional conflict	Decisional Conflict Scale (16 items) [52]; satisfaction with the chosen method [64]	
**Tertiary**			Assessed 1-year prebaseline, at baseline, 3 months, and 6 months (all women; n=180)
	Viral suppression	Viral suppression, defined as viral load below limit of detection per assay used	
	Medication refills	Missed doses; report of medication refills/pharmacy pick up (WWH^c^ on oral ART^d^)	
	Clinic attendance	Missed or cancelled medical visits (<2 visits in a 6-month period for oral ART; missed monthly visit for LAI^e^ ART)	
	ART modality	Adoption of LAI among patients who are virally suppressed	
**Moderators**			Assessed at baseline
	Sociodemographics	Race/ethnicity, age, housing stability, education, employment, income, distance from clinic, relationship status, children	
	Depression/anxiety	PHQ-8^f^ (depression) [65]; GAD-7^g^ [66]	
	Substance use	ASSIST^h^ [67], an 8-item measure of problematic substance use	
	Stigma/discrimination	MDS^i^ to measure racial discrimination [68]; HIV-related stigma	
	Self-efficacy	HIV-ASES^j^ [38]	
	ART-related knowledge	Adaptation of Feldman’s [69] scale of oral ART knowledge; BMQ^k^ [70]	

^a^*i.ARTs*: i.ART+support.

^b^CSQ-8: 8-item Client Satisfaction Questionnaire.

^c^WWH: women with HIV.

^d^ART: antiretroviral therapy.

^e^LAI: long-acting injectable.

^f^PHQ-8: 8-item Patient Health Questionnaire.

^g^GAD-7: 7-item General Anxiety Disorder scale.

^h^ASSIST: Alcohol, Smoking and Substance Involvement Screening Test.

^i^MDS: 10-item Multiple Discrimination Scale.

^j^HIV-ASES: HIV Treatment Adherence Self-Efficacy Scale.

^k^BMQ-18: 18-item Beliefs and Medicines Questionnaire.

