While preliminary research suggests that most WWH would prefer LAI ART over their current daily oral medication [18], this research has also identified multilevel barriers to LAI ART uptake. At the *individual level*, these include women’s concerns about side effects, pregnancy-related interactions, and drug resistance if LAI ART is discontinued without oral ART initiation; at the *clinic level*, barriers include medical mistrust due to historic sterilization campaigns [19] and lack of provider knowledge and willingness to offer LAI ART; and at the *structural level*, barriers include gender-specific socioeconomic inequalities and dynamics such as low-wage employment with unstable scheduling, lack of transportation, and care-taking responsibilities. Furthermore, FDA indication still requires viral suppression via oral ART prior to initiating LAI. These multilevel barriers could all complicate the frequent visits that LAI ART administration will require [18,20-23]. WWH and providers may benefit from tools and strategies that help them to identify and address barriers that prevent uptake of, and adherence to, LAI ART.

Shared decision making in medical settings is often accomplished using patient decision aids. These evidence-based tools promote equity in medicine by increasing patients’ knowledge, decision-making power [24,25], and health outcomes [26-28]. This approach can also lower medical paternalism [24,29-31]. Patient decision aids can improve medication adherence directly [32], as well as through mediating factors (eg, patient satisfaction [33-35], efficacy [36-38], and communication) [33,39,40]. These tools are ideal for preference-sensitive decisions with multiple options [41,42]; however, no patient decision aids yet exist to facilitate women’s choice between HIV treatment modalities. New tools are urgently needed to ensure the successful and equitable integration of new technologies such as LAI ART into clinical settings [43].

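### The tertiary EMR measures do not reliably separate a woman who stopped LAI and is on no ART from one still on LAI or back on oral ART

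*Protocol article*

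**What the plan says.** The Assessments section sets out the chart abstraction. It covers three items without restricting them to one treatment: "Study staff will abstract data on viral suppression (all women), ART modality, clinic attendance (all women". Refills are the exception and are listed as "medication refill data (women on oral ART". Table 2 repeats that restriction beside its definition, "Missed doses; report of medication refills/pharmacy pick up", and Study Outcomes and Measures repeats it again. The window is fixed: "Abstraction will include data from 1-year prebaseline to 6 months postbaseline". Table 2 gives the time points for the tertiary outcomes: "Assessed 1-year prebaseline, at baseline, 3 months, and 6 months (all women; n=180".

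Three definitions matter here:

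- **Modality** (Table 2): "Adoption of LAI among patients who are virally suppressed".
- **Attendance** (Table 2): "<2 visits in a 6-month period for oral ART; missed monthly visit for LAI".
- **Suppression** (Study Outcomes and Measures): the reading at the latest visit within the preceding 6 months.

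The Analysis section adds a between-arm count of women who change modality after baseline, used to judge how accurately the tool matches women to a treatment. The Introduction lists, among women's concerns about LAI, "drug resistance if LAI ART is discontinued without oral ART initiation". The Introduction and Expected Challenges both report that a bimonthly LAI product is approved; Expected Challenges gives the interval as every 8 weeks.

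**The concern.** The tool generates a suggested modality, so it can influence who starts LAI. Once a woman has started, the informative question is whether she is still covered: by injections, by oral ART after a switch, or by neither. The tertiary measures are built around starting LAI and around being on one of two treatments. None of them names stopping LAI or being on no ART.

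At stake is how the adoption result can be read. An adoption proportion that combines women still on treatment with women who have lapsed says less about the quality of the match than the Analysis section wants from it. There is a second, related problem. Whether a woman is on oral ART after baseline is a post-randomization state that the intervention may affect. A refill comparison limited to that group is therefore not a comparison of the arms as randomized, although the plan's primary analysis is by intent to treat.

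**Working it through.** The plan gives no figure on this point to reproduce; its power statement concerns decisional conflict and does not enter. The check is to take three women who all enter on oral ART, start LAI after baseline and are suppressed at month 3, and apply each stated measure at month 6. Entry on oral ART is an assumption.

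| Measure as written | Still on LAI | Stopped LAI, back on oral ART | Stopped LAI, on nothing |
|---|---|---|---|
| Modality (LAI adoption) | Adopter | Adopter | Adopter |
| Count of women changing modality | Already counted on starting LAI | Already counted | Already counted |
| Refills | Not abstracted | Abstracted if she is classed as on oral ART | Not abstracted |
| Suppression, latest visit in prior 6 months | Month 3 or later | Month 3 or later | May be the month 3 reading, before the stop |
| Attendance | LAI rule | Oral rule if reclassified, LAI rule if not | LAI rule if still classed as LAI; otherwise no rule |

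1. **Suppression.** At month 6 the look-back runs from month 0 to month 6. A month 3 reading qualifies if there is no later one. With visits about every 3 months, as Assessments states, a woman who lapses after month 3 and does not return has no later reading.

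2. **Refills.** Refills are sought only for a woman already classed as on oral ART, so they cannot verify that classification. If her chart moves her to oral ART and she never fills, the refill measure can show it. If her chart still lists LAI, or lists nothing, no fills are sought and their absence is not recorded.

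3. **Attendance.** This is the main remaining signal for the third woman. Over 6 months a monthly schedule gives 6 visits. An 8-week schedule gives about 26/8 = 3.25, so about 3, ignoring any initiation visits. Applied literally, the monthly rule flags about 6 − 3 = 3 of 6 months for a woman who is fully on schedule with the bimonthly product. No injection dates are listed that would tell her apart from a woman who has stopped.

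4. **Size per woman.** With 90 women per arm, one woman carried forward as suppressed shifts that arm's suppression proportion by 1/90 = 1.1 percentage points. For adoption the denominator is the virally suppressed women, at most 90, so one woman counts for at least 1.1 points.

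**The case against.** The strongest reply is that the data are largely being collected. Modality, attendance and viral load are abstracted to month 6, so a woman who stops LAI can show up through her modality record, missed injection visits or loss of suppression. A woman recorded as back on oral ART would have her refills abstracted, so missed LAI visits with no oral record is already a distinguishable pattern. The outcomes are exploratory, in a pilot whose primary outcomes are feasibility, acceptability and usability. A journal article may also leave coding categories to an abstraction form or analysis plan.

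Most of this stands as a limit on the point. It does not remove it. The pattern has to be inferred, depends on the chart's modality entry being current, and is blurred by an attendance rule that fits only one of the two approved schedules. The restriction of refills is a stated choice, made in three places; it is not detail lost in condensing. An analysis plan can define categories but cannot supply fills that were never abstracted.

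A reader might infer more than the text supports:

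- **That the protocol declares resistance after stopping LAI a key risk and then ignores it.** The Introduction lists it as a concern of women and a barrier to uptake. It is not called a key risk and is not a trial endpoint.
- **That women on no treatment are counted nowhere, or that the tool makes lapses more frequent.** The first is contradicted by the partial signals above. The second has no support: the tool may suggest either modality and adds adherence suggestions, and control-arm providers may also steer the choice.
- **That the 6-month window is an error.** It is a reasoned choice, tied to visits about every 3 months. Lapses after month 6 are unseen, but following only LAI starters for longer would select on a post-randomization group with unequal follow-up.

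**Conclusion.** The point holds as a gap in definition and in the scope of abstraction for exploratory outcomes. It is not a failure to collect relevant data. As written, a woman who starts LAI, is suppressed at month 3 and lapses before month 6 can be reported as a suppressed LAI adopter, and no outcome in Table 2 assigns her to no treatment. The number of such women cannot be derived, because the documents give neither expected LAI uptake nor a stopping rate; only the effect of each one, about 1.1 points on an arm's suppression proportion, follows from the text. The conclusion assumes that Table 2's definitions are applied literally and that her chart does not itself record that she is on no ART. The decisional conflict analysis and its sample size are unaffected.

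**What to change.** Within the planned 6-month window:

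1. Abstract oral ART fills for all 180 women, and injection dates for every woman who starts LAI.
2. Code treatment status at 3 and 6 months as oral with a current fill, LAI with a current injection under the schedule recorded in her chart, or neither. Define what counts as current before data are seen.
3. Report neither by randomized arm, alongside LAI adoption. This gives a status for every randomized woman and avoids conditioning on modality after baseline.
4. Reconcile the monthly wording of the LAI attendance measure with the article's own statements that a bimonthly product is approved.

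Reasons for stopping and any resistance result in the chart are optional additions. No abstraction beyond month 6 is needed for this point.

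The cost is modest extra chart-abstraction time, with no added visits, tests or participants. The change is best made before Phase 3 opens, because the EMR release form is part of informed consent and must cover these fields.
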